#### KMMS quality review

Systematic and retrospective investigation of patient medical records has long been used in quality assessment and improvement studies, professional education and training, and as an assessment of patient care initiatives [26–29]. This study will review the quality and appropriateness of KMMS and DMT assessments from all sites via two separate panel processes (Additional files 5 and 6).

The panels will convene every 3 months and will consist of a minimum of four members who have relevant clinical expertise and are sufficiently impartial to the study [29], i.e. health professionals not engaged in the administration of the KMMS or the DMT. The panels will be convened by a member of the research team. A minimum of nine and maximum of 12 files will be selected by the KMMS research team and reviewed by the panel at each meeting. A quota sampling strategy [26] will be used to select the files to ensure the panels are reviewing a spread of KMMS/DMT results, antenatal and postnatal women, health professionals, and health services.

Overall findings from each panel will be disseminated back to partner health services as a quality initiative. Where required, additional training and support will be offered to health services to ensure that Aboriginal and Torres Strait Islander women are receiving appropriate care and support via the KMMS and the medical files and records reflect the service provided.

#### Acceptability of the KMMS

User acceptability is a multi-faceted construct that investigates if and how recipients or administrators of a healthcare intervention consider it to be appropriate [30, 31]. The study will assess key domains of user acceptability (Table 1) using a range of methods including questionaries and qualitative interviewing.

**Table 1 Tab1:** Kimberley Mum’s Mood Scale user acceptability measures adapted from El-Den et al. [30] and Sekhon et al. [31]

User Acceptability measure	Patient	Staff
Tool Content		
Overall acceptability including views on cultural security	✓	✓
Clarity/understanding (purpose, process, questions, rating scales)	✓	✓
Content and concepts	✓	✓
Structure/format and length	✓	✓
Language, terminology and graphics	✓	✓
Process		
Quality of relationship between patient and administrator	✓	✓
Appropriateness of screening location and timeframe	✓	✓
Perceived effectiveness of the tool in achieving its purpose	✓	✓
Perceived benefits/disadvantages of using the tool	✓	✓
Levels of confidence in using the screening tool	✘	✓
Barriers to use, burden of completing, opportunity costs, workload	✓	✓
Other impacting factors		
Perception of importance of screening for perinatal depression and anxiety	✓	✓
Perceptions of prevalence of perinatal depression and anxiety	✓	✓
Perceptions of availability and adequacy of follow up support and treatment	✓	✓
Satisfaction with training	✘	✓
Information, communication and technology requirements	✘	✓
Familiarity with and number of times using the tool	✓	✓

Women consented to the KMMS study will be asked to complete a 5-item paper-based feedback questionnaire immediately after the administration of their first KMMS. This questionnaire will assess participants’ experience with the KMMS tool, specifically exploring perceptions of tool content (Table 1). Additionally, a subset of women (*n* = 6–12 per KMMS region) will be invited to participate in a face-to-face in-depth interview approximately 3–6 months after administration of their first KMMS. The interviews will be no longer than 1 h in duration and will use a methodological approach of phenomenology to explore experiences of completing the KMMS [30, 31]. Recruitment for in-depth interviewing will occur by following up with those women who expressed interest in an interview by leaving their details on the KMMS feedback questionnaire. Additional measures of purposive sampling such as the study team attending mums and bubs groups or playgroups may result in further recruitment. Participants will provide written consent prior to their involvement in the interviews.

Health professionals will also provide data on the acceptability of the KMMS training and KMMS tool. At the time of training, all health professionals will be asked to complete a paper-based feedback questionnaire. This feedback will relate to the health professional’s experience of the training, including their perceptions of the significance and prevalence of perinatal depression and anxiety in the region in which they work. All health professionals who have been trained and have subsequently administered the KMMS will be asked to complete an online questionnaire 6 months post KMMS administrator training. The questionnaire will assess KMMS use and the health professional’s experience of the KMMS as a feature of clinical care.

Additionally, a subset of KMMS-administrator health professionals (*n* = 6–12 per KMMS region) will be invited to complete an in-depth interview (in person or by phone) 6 or 12 months post administrator training. Recruitment will occur via phone calls to all trained administrators. Interviews will be no longer than 1 h in duration and will explore user acceptability measures identified in Table 1.

All user acceptability data will be anonymous (questionnaries) or de-identified (in-depth interviews) and participants confidentiality will be maintained at all times.

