#### Training perinatal health professionals

All perinatal health professionals in partner health services will be offered approximately 2–3 h of KMMS training. Training will be divided into three sessions:
KMMS in-service (50 min) designed to be delivered to all clinical staff. This training will provide information and awareness on perinatal mental health and wellness, provide an overview of the KMMS and ensure that all clinical staff are aware of the KMMS project.KMMS administrator training (1.5–2 h) designed to be delivered to health professionals who will be administering the KMMS. This will provide an in-depth explanation of how to use the KMMS, determining the overall risk level and how to recruit and consent women to the study.KMMS Diagnosis and Management Tool training (50 min). GPs and mental health professionals will be provided with specialist training in how to use the standard reference assessment, called the KMMS diagnosis and management tool (DMT; Additional file 4). This training will provide an overview of the KMMS screening process, the origins of the DMT and how to use the DMT as part of diagnosis and management of perinatal depression and/or anxiety.

All training will be provided face-to-face or via online classroom workshops. For health professionals involved in the KMMS administrator or DMT training, support and mentoring in using the KMMS tools will be available for the duration of the study.

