#### Kimberley implementation study

It is recognised that health service implementation is a complex undertaking with many promising research findings failing to translate into improved patient outcomes [22, 23]. Using the Dynamic Sustainability Framework (DSF) [24] we seek to explore and report on the process of implementation. This includes an examination of how the intervention (components, practitioners, outcomes, delivery platform), practice setting (staffing, organisational culture, information systems, business model, training and supervision), and ecological settings (population characteristics, policy, regulation, funding) enable or inhibit implementation of the KMMS into routine clinical care. Specific to the DSF is the expectation that “change is a constant and thus the success of an intervention to be sustained over time lies in the measured, negotiated, and reciprocal fit of an intervention within a practice setting and the practice setting within the larger ecological system” [24]. The DSF posits that ‘fit’ involves the way an intervention is delivered, the characteristics of patients, providers and settings, and the broader system within which health care is situated [24]. The DSF’s recognition and embrace of the constancy of change is compelling and speaks to the realities of the Northern Australian health workforce which is characterised by high turnover, low stability and high use of temporary staffing [25]. Similarly, the emphasis the DSF places on ‘fit’ seems a pertinent starting point for evaluating the process of implementing the KMMS across the geographically large and culturally diverse region of the Kimberley. The learnings and reflections from the process of implementation will be shared with partner health services and the KAHPF, and submitted to relevant peer reviewed journals and national interest bodies contributing to the science of ‘what works’ in the validation and implementation of Aboriginal and Torres Strait Islander health improvement initiatives.

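### The 6-month staff questionnaire goes only to trained staff who have used the KMMS, so the one post-training staff survey cannot show how many never used it, or why

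*Protocol article*

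**What the plan says.** The protocol article, *Acceptability of the KMMS*, describes three sources of staff data.

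- **At training.** "At the time of training, all health professionals will be asked to complete a paper-based feedback questionnaire". It covers the training itself and how staff see the significance and prevalence of perinatal depression and anxiety in their region.
- **At 6 months.** "All health professionals who have been trained and have subsequently administered the KMMS will be asked to complete an online questionnaire 6 months post" administrator training. On content: "The questionnaire will assess KMMS use and the health professional’s experience of the KMMS as a feature of clinical care".
- **Interviews at 6 or 12 months.** A subset of 6–12 KMMS administrators per region is invited. "Recruitment will occur via phone calls to all trained administrators", and the interviews "will explore user acceptability measures identified in Table 1".

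Table 1 in the same section ticks, for staff, "Barriers to use, burden of completing, opportunity costs, workload". It also ticks confidence in using the tool and how often it has been used.

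*Kimberley implementation study* sets out to examine the factors that "enable or inhibit implementation of the KMMS into routine clinical care". *Outcome measures* lists acceptability (all sites) and implementation (Kimberley) as primary outcomes. *Qualitative analysis* names the user acceptability data as one input to the process evaluation.

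**The concern.** The eligibility rule for the 6-month survey selects respondents on adoption, and adoption is part of what the implementation outcome is meant to explain. Staff who were trained but never administered the KMMS, whether for lack of time or confidence, from disagreement with the tool or because they moved post, receive no follow-up survey. For some of them the barriers in Table 1 may have been decisive.

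Such staff are foreseeable. *Kimberley implementation study* itself describes a workforce with high turnover and much temporary staffing. *Study populations* defines sample frame B by the provision of perinatal care and does not require KMMS use, so the survey's frame is narrower than the study's own staff population.

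At stake is whether the survey can inform the inhibiting side of the implementation question. If it cannot, its findings on barriers describe only barriers that were overcome at least once.

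**Working it through.** No sample size, rate or margin is involved, and the article states no figure to reproduce. The check sets the sources side by side and asks what each can say about trained staff who did not use the KMMS.

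**1. What the 6-month survey can observe.** Let N be the number given administrator training and U the number of those who later administered the KMMS. The survey frame is U. Among its respondents the proportion who have ever used the tool is 1 by construction, so the survey carries no information on (N − U)/N or on the reasons of the N − U. Yet one of its stated purposes is to assess KMMS use. Within its frame it can measure frequency of use but not non-use.

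**2. What the other sources add.**

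| Source | Open to trained non-users? | Records why they did not use it? |
|---|---|---|
| Questionnaire at training | Yes | No: completed before any use, on training and perceived importance |
| 6-month online questionnaire | No | No |
| Staff interviews | Yes, by the recruitment sentence | Possibly, for whoever takes part; no provision for non-users stated |
| Completion rates, consultations, field notes, meeting minutes, training calendars | Indirectly | Not systematically, and not from the individuals concerned |

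**3. Reading the interview frame.** The interviewees are labelled KMMS administrators, which could be taken to mean users only. But recruitment is by calls to all trained administrators, and *Training perinatal health professionals* describes administrator training as "designed to be delivered to health professionals who will be administering the KMMS". That is an intention at the time of training, so a trained administrator need not have administered anything. On this reading non-users are eligible.

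**4. Size of the interview sample.** 6–12 per region in three regions gives 3 × 6 = 18 to 3 × 12 = 36 in total, and 6–12 in the Kimberley, the only region with an implementation outcome. With no stated provision for non-users, the number of them could be zero.

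**5. Size of any bias.** For an item that both groups could answer, let p = U/N, and let a_u and a_n be the favourable proportions among users and non-users. The users-only figure differs from the figure for all trained staff by

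a_u − [p·a_u + (1 − p)·a_n] = (1 − p)(a_u − a_n).

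The article gives none of p, a_u or a_n. The sign depends on a_u − a_n, which a users-only survey cannot reveal.

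**The case against.** The strongest reply is that the survey is a supplement. *Outcome measures* says acceptability is assessed mainly by phenomenological methods, with descriptive statistics in support. Implementation is a process evaluation with several sources that do not depend on an individual having used the tool. Quantitative uptake data exist: *Qualitative analysis* lists rates of completed KMMS and DMT, and *Kimberley revalidation study* adds de-identified counts, scores and basic demographics for all KMMS assessments. All of this stands. It rules out a stronger reading that a reader might infer, namely that non-adopters are removed from two primary outcomes, or that the inhibiting side is left without quantitative data.

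A second reply is that the construct is user acceptability, and someone who has never used the tool has no experience of it in care to rate. This also stands for ratings of experience, and the fix respects it. It does not cover barriers or confidence, which a trained non-user can report.

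A third reply is that applying the rule requires knowing who has used the tool, so the share of non-users might be obtained from records. That is possible, but the article does not say how use is established or that this share will be reported, and records would not supply reasons.

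A reader might also infer that acceptability will be overstated by some definite amount. For example, assuming 70% uptake and favourable ratings of 85% among users and 40% among non-users gives (1 − 0.70) × (85 − 40) = 13.5 points; at 50% uptake it gives 22.5. Every input is assumed. With equal ratings the gap is zero, and non-use caused by staff turnover need not mean low acceptance. The article also sets no percentage endpoint for acceptability among all trained staff. These figures show the mechanism and are not an estimate.

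**Conclusion.** The point holds in a limited form. The only staff survey after training is restricted to adopters. Whatever it yields on use, confidence and barriers comes from users alone, and it cannot show what share of trained staff never used the KMMS or why. Its results nevertheless enter the acceptability outcome directly and the Kimberley implementation outcome through the process evaluation.

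Non-adopters remain represented through the training questionnaire, potentially the interviews, and indirect process data. None of these systematically collects their reasons. The documents do not allow the size or direction of any bias to be estimated.

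The conclusion assumes that some trained administrators will not have used the KMMS by 6 months, which the article's account of the workforce makes plausible but does not quantify. It also takes the recruitment sentence for the interviews at face value. This is a cheap improvement to the study's ability to answer its own implementation question; it does not invalidate either outcome.

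**What to change.** In *Acceptability of the KMMS*:

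- Send the 6-month online questionnaire to everyone who completed KMMS administrator training.
- Open with a question on whether the respondent has administered the KMMS since training. Route those who have not to a short branch on reasons, barriers and confidence.
- Report the proportion of trained respondents who ever used the KMMS, alongside the number invited and the response rate.
- Keep ratings of experience and acceptability for users. Report barriers for users and non-users separately.
- State that the staff interviews include trained non-users, which also settles the ambiguous label.

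The cost is a few extra online items and some extra invitations. A contact list should already exist, since all trained administrators are to be phoned for the interviews. The main downside is a probably lower response among non-users, so the proportion who ever used the tool may be overstated among respondents and should be read with the response rate.

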### Outcome measures

Primary outcomes:
Diagnostic accuracy of the KMMS as a screening tool for perinatal depression and anxiety assessed by comparing results of the KMMS with the DMT.Acceptability of the KMMS for all sites assessed primarily through the qualitative methodology of phenomenology supplemented with descriptive statistical analysis.Implementation of the KMMS in the Kimberley assessed using a process evaluation methodology framed by the DSF.

Secondary outcomes:
Patterns of change identified in KMMS risk for women who have more than one KMMS assessment.Variations in DMT diagnosis determined with KMMS assessment overall score based on if the DMT was conducted blinded or not.KMMS quality and appropriateness identified based on the findings of the KMMS quality review panels.

### Sample size calculation

We plan to recruit an equal number of antenatal and postnatal women. The data from antenatal and postnatal women will be pooled for the main analysis, as there was no significant difference in KMMS or study GP assessments between antenatal and postnatal participants in the Kimberley validation study [13]. If there is no significant difference between the data from the three regions, these data will also be pooled.

For the validation/revalidation study, assuming there is a minimum sensitivity of 83% for screening for perinatal depression and anxiety and prevalence is at least 25% (based on the Kimberley validation study), using calculations by Buderer [32] a sample size of 868 paired KMMS and DMT assessments will detect a two-tailed 95% CI with a maximum width of ±5% (i.e., if sensitivity 83, 95% CI 78–88%). This is at the upper end of reported sensitivities for the EPDS compared to a reference standard assessment (59–100%) [33].

Based on the Kimberley validation study [13], we expect 65% of KMMS assessments to be referred for DMT and that at least 75% of the participants who are referred will have both the KMMS and DMT assessments completed (i.e., require 1780 KMMS to obtain 868 paired assessments). For the secondary analysis to determine changes in KMMS risk, we aim to assess as many participants as possible both antenatally and postnatally. As a conservative estimate, we will assume that at least 60% of participants will have KMMS administered at both time points. Recruiting 890 antenatal women (50% of the 1780 KMMS required) should provide at least 534 paired antenatal/postnatal KMMS assessments. In addition, approximately 356 women will be recruited postnatally to ensure that we have 890 antenatal and 890 postnatal KMMS assessments required for the main sample size calculation. Therefore, we initially aimed to recruit 1246 women (890 in the antenatal period and 356 women postnatally) to provide 868 paired KMMS / DMT assessments and 534 paired antenatal/postnatal KMMS assessments.

The complexity of establishing a partnership project across three remote regional areas has taken longer than anticipated; as such a revised sample size is 700 women across all three regions. Assuming 442 of the 700 women have paired KMMS and DMT assessments, this would allow us to detect a two-tailed 95% CI with a maximum width of ±7% (i.e., if sensitivity 83, 95% CI 76–90%).

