#### Further clinical assessment

The DMT is the standard reference assessment for all further KMMS clinical assessments. Diagnosis is based on the Diagnostic and Statistical Manual of Mental Disorders (DSM IV) criteria for depressive and anxiety disorders [20] and severity (i.e. low, moderate, high) on the GP Mental State Examination [21]. Participants who are referred for an assessment using the DMT will be assessed as soon as practicable after the KMMS is administered. For those diagnosed with perinatal depression and/or anxiety, a follow-up management plan will be negotiated between the participant and the GP / mental health professional, ensuring appropriate support, referrals and treatment is discussed and agreed upon by both the woman and the health care professional.

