#### Pilbara and Far North Queensland validation study

In the Pilbara and FNQ selected health services have agreed to trial the KMMS instead of the EPDS to screen for perinatal depression and anxiety. Partner health services will ask perinatal women for consent to participate in the study. This includes completing the KMMS and providing feedback on the screening tool. All women scoring moderate or high on the KMMS and a sample of women scoring low on the KMMS will be referred for a further clinical assessment using the DMT. As in the Kimberley, the KMMS will be offered in accordance with the national EPDS screening schedule [4] and rescreening will involve completing a new Part 1 and continuing the yarn in the original Part 2.

Women who do not consent to the study can use the KMMS, but no identifying information will be collected on these women.

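### The sample size counts two KMMS/DMT pairs from one woman as independent, so the planned precision is somewhat optimistic, and the revised 442 of 700 women does not fit the protocol's own yield

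*Protocol article*

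**What the plan says.** The Sample size calculation section states that "The data from antenatal and postnatal women will be pooled for the main analysis". The precision target is expressed in assessments: "a sample size of 868 paired KMMS and DMT assessments will detect a two-tailed 95% CI with a maximum width of ±5" percentage points. To supply them, 1780 KMMS are needed. These are to come from 890 women recruited antenatally, 60% of whom (534) are screened again postnatally, and in addition "approximately 356 women will be recruited postnatally to ensure that we have 890 antenatal and 890 postnatal KMMS assessments". The total is 1246 women, and the repeat screens count towards the main calculation.

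The same section then revises the target to 700 women, 442 of whom are assumed to have a KMMS/DMT pair, for ±7%.

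On repeat screens, the Pilbara and Far North Queensland section says "rescreening will involve completing a new Part 1 and continuing the yarn in the original Part 2", and the section on the KMMS describes the same practice for the Kimberley. Under Further clinical assessment, "For those diagnosed with perinatal depression and/or anxiety, a follow-up management plan will be negotiated". The Blinding section expects many DMT assessors to see the KMMS result.

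**The concern.** Two pairs from the same woman carry less information than pairs from two women whenever her results are positively correlated. A calculation that counts both in full overstates the precision of sensitivity, a primary outcome.

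There is also a question of what the repeat pair measures. The second KMMS carries the earlier Part 2 forward, and overall risk is a clinician's judgement on both parts. If the woman was diagnosed at her first DMT, she already has a management plan. Her second pair then reflects re-recognition or response to care as well as detection. Pooled with first pairs, it blurs what the reported sensitivity describes.

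Finally, if the current target can be met only by counting repeats, its wording per woman does not settle the matter.

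**Working it through.** **Inputs, all from Sample size calculation.** Sensitivity 0.83 ("assuming there is a minimum sensitivity of 83% for screening for perinatal depression and anxiety"); prevalence 0.25 ("prevalence is at least 25% (based on the Kimberley validation study"); 65% of KMMS referred and at least 75% of those referred completed ("we expect 65% of KMMS assessments to be referred for DMT and that at least 75% of the participants who are referred"); 60% of antenatal recruits rescreened. Within-woman correlation ρ and the persistence of diagnosis between screens are not given. I assume ρ of 0.3 to 0.7, and that half or all of those diagnosed at the first pair are again cases at the second.

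**1. The plan's figures reproduce under independence.**
- Cases needed: 1.96² × 0.83 × 0.17 / 0.05² = 216.8, rounded up to 217; 217 / 0.25 = 868 pairs.
- Yield per KMMS: 0.65 × 0.75 = 0.4875; 868 / 0.4875 ≈ 1780 KMMS.
- Women: 0.60 × 890 = 534; 890 − 534 = 356; 890 + 356 = 1246, or 1780 / 1246 = 1.43 KMMS per woman.
- Revised: 1.96² × 0.83 × 0.17 / 0.07² = 110.6; 110.6 / 0.25 ≈ 442 pairs.

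No design effect enters anywhere.

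**2. Effect of repeats on the ±5%.** If DMT completion is independent between screens, 534 × 0.4875² ≈ 127 women give two pairs. Sensitivity uses only cases, so the quantity that matters is D2, the number of women who are cases at both pairs. The design effect is 1 + ρ × 2·D2 / 217.

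| Persistence | D2 | 2·D2/217 | Design effect, ρ 0.3–0.7 | Half-width |
|---|---|---|---|---|
| Half | 15.9 | 0.146 | 1.04–1.10 | ±5.1 to 5.25% |
| All | 31.7 | 0.292 | 1.09–1.20 | ±5.2 to 5.5% |

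If DMT completion were fully concordant within women, 534 × 0.4875 ≈ 260 women would give two pairs. With full persistence and ρ = 0.5, the half-width would be ±5.7%.

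**3. The revised target against the stated yield.** 442 / 700 = 63.1%, against 48.75% per KMMS. At the earlier screening pattern, 700 women give 700 × 1.43 = 1000 KMMS: 500 antenatal recruits, 300 of them rescreened, and 200 postnatal recruits. That yields 1000 × 0.4875 ≈ 488 pairs. Under independent completion 300 × 0.4875² ≈ 71 women supply two, so 488 − 71 ≈ 416 women (before rounding) have at least one. Half-width is 1.96 × √(0.83 × 0.17 / (0.25 × pairs)), times the square root of the design effect where clustered. The multiplier on ρ is again 0.146 or 0.292.

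| How 700 women are counted | Pairs | Half-width |
|---|---|---|
| As printed | 442 | ±7.0% |
| One screen each | 341 | ±8.0% |
| 1.43 screens, one pair per woman | 416 | ±7.2% |
| 1.43 screens, all pairs, taken as independent | 488 | ±6.7% |
| All pairs, clustered, half persist | 488 | ±6.8 to 7.0% |
| All pairs, clustered, all persist | 488 | ±7.0 to 7.3% |

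With one screen each, 442 would require 442 / (700 × 0.65) = 97% completion among those referred.

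**4. Possible shift in sensitivity.** Under the two persistence assumptions, second pairs in women already diagnosed are 15.9 / 217 = 7.3% or 31.7 / 217 = 14.6% of case pairs. With 0.83 at other pairs, pooled sensitivity is 0.839 to 0.855 if repeat sensitivity is 0.95 to 1.00, and 0.811 to 0.820 if it is 0.70. The documents give no repeat-screen sensitivity.

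**The case against.** Four objections deserve an answer.

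*The protocol does not say that the analysis will treat pairs as independent.* This stands. A reader might infer it from the pooling sentence, but that sentence concerns antenatal and postnatal groups, and the Quantitative analysis section names no interval method. An analysis plan not shown could cluster by woman or take one pair each. That section already treats repeats as paired for change in risk, using McNemar's test. The criticism is of the planning calculation.

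*The 868 target is superseded, and the 442 is worded per woman.* The wording is as claimed, and read literally it contains no repeats. But the stated rates do not produce 442 women with a pair: they give 341 with one screen each, or about 416 at the earlier rescreening pattern. The 75% and 60% are given as minimums, so 442 is not impossible, but no higher rate is stated. If all 488 pairs count and are clustered, ±7% is roughly attainable, so the revised precision is not far wrong. What is unresolved is what it counts.

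*Sensitivity is not shown to be inflated.* This also stands. A reader might infer upward bias from the carried-over Part 2, a diagnosis on record and incomplete blinding. Yet management between screens could equally lower detection at the repeat, and the sign depends on a quantity the documents do not give. Nor do repeat screens in general follow a diagnosis: that holds only for women who had a first DMT and were diagnosed.

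*Accuracy per screen as delivered is a legitimate target.* It is. The objectives ask for real-world performance, and rescreening is part of how the KMMS is used. This argues against imposing first pairs as the only primary set. It does not remove the need to allow for clustering.

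**Conclusion.** The point holds for the sample size text and is modest in size. Counting 534 women twice in a formula for independent pairs makes ±5.0% about ±5.1 to 5.25% with half persistence, or ±5.2 to 5.5% with full persistence. Both ranges assume independent DMT completion and correlation of 0.3 to 0.7; the loss is larger if completion is concordant within women and smaller if few diagnoses persist.

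The current 442 of 700 does not agree with the 65% × 75% yield unless repeat pairs are counted, which conflicts with its wording per woman. The figure of 416 women rests on independent completion and the earlier 60% rescreening rate.

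Repeat pairs in women diagnosed at their first DMT may move pooled sensitivity by one or two percentage points either way on these assumptions. The documents support no firmer statement on direction or size.

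**What to change.** 1. State the unit of analysis for diagnostic accuracy, and whether repeat pairs count towards 442.
2. If they count, compute the intervals for sensitivity and specificity with clustering by woman (GEE, cluster-robust standard errors, or a bootstrap that resamples women).
3. Report accuracy for each woman's first pair alongside all pairs, and flag pairs that follow an earlier DMT diagnosis.
4. Restate the 442 of 700 and the ±7% so that they agree with the 65% × 75% yield, or give the different rates on which they rest.

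No new data collection is needed beyond linking pairs within woman, which the planned analysis of change in risk already requires. The cost is a slightly wider stated interval and a little more analysis. Reporting first pairs as well as all pairs avoids a forced choice between the two targets.
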